## Abstract

**Background:**

Despite a number of recommended strategies, effective treatment of migraine remains elusive. Given the role of oxidative stress in the pathogenesis of migraine, selenium, as an antioxidant nutrient, may have a beneficial effect on migraine outcomes. However, no study has explored the effects of selenium supplementation on migraine symptoms, oxidative stress biomarkers, and mental health. Therefore, this randomized, double-blinded, placebo-controlled clinical trial aims to examine the effects of selenium supplementation among migraine patients.

**Methods:**

**S**eventy-two migraine patients will receive either 200 µg/day selenium supplement (*n* = 36) or placebo (*n* = 36) for 12 weeks in a randomized, double-blinded, placebo-controlled study. The severity, frequency, and duration of headaches, mental health indices including depression, anxiety, and distress, and quality of life, as well as biomarkers of oxidative stress such as nitric oxide (NO), malondialdehyde (MDA), total antioxidant capacity (TAC), and total oxidant status (TOS), will be measured at the baseline and end of the study. The intention-to-treat (ITT) approach will be used to estimate missing values. One-way analysis of covariance (ANCOVA) will be performed to detect the effect of selenium supplementation on outcome variables.

**Discussion:**

Oxidative stress is recognized as a key contributor to migraine pathogenesis. Selenium is an essential trace element with antioxidant properties, capable of crossing the blood–brain barrier (BBB), holding promise to alleviate the oxidative stress and neurotoxicity. Thus, selenium may beneficially affect clinical symptoms and oxidative stress as well as the quality of life in migraine patients.

**Trial registration:**

This trial was registered in the Iranian Registry of Clinical Trials (https://www.irct.ir/) on 27 May 2023 with the code number IRCT20121216011763N60.

**Supplementary Information:**

The online version contains supplementary material available at 10.1186/s13063-024-08018-8.

## Introduction

### Background and rationale {6a}

Migraine is a prevalent neurological disorder affecting approximately 14–15% of the global population [1], which imposes a substantial burden on public health. In Iran, the prevalence of migraine is estimated to be 15.1% among adults [2]. Migraine is also known as the second leading cause of disability in individuals below 50 years, particularly among women, and is associated with an increased risk of different psychological disorders, including depression and anxiety [3, 4]. Migraine patients experience moderate to severe, throbbing and unilateral headaches, which are frequently accompanied by other symptoms, such as vomiting, nausea, photophobia, and phonophobia [5]. Accordingly, finding effective strategies for the management of migraine is urgently required.

Despite the availability of various pharmacotherapies for migraine management, including beta-blockers, calcium channel antagonists, triptans, antipsychotics, antiepileptics, and botulinum neurotoxins [6], their efficacy is often limited, and accompanied by several side effects [7]. Therefore, complementary therapies such as vitamin/mineral supplementation, acupuncture, and herbal medicine have received more attention. Recent evidence indicates that oxidative stress and inflammation play a key role in the pathophysiology of migraine headaches by stimulating abnormal activation of nociceptive neurons. In addition, migraine headaches are recognized as a neuro-protective response to elevated oxidative stress and inflammation in the brain [8]. Previous studies have shown that antioxidants such as vitamin C, zinc, and coenzyme Q10 benefit oxidative stress and clinical symptoms of migraine patients [9].

Of different antioxidants, selenium is of particular interest, exerting its biological functions through selenoproteins such as glutathione peroxidase, iodothyronine deiodinases, and thioredoxin reductase [10, 11]. A number of studies have shown that selenium plays a key role in the normal physiological function of the brain [12]. Furthermore, the established antioxidant activity of selenoproteins in the central nervous system suggests that lower selenium levels can be associated with brain damage [13]. Indeed, a recent case–control study showed that migraine patients have lower selenium levels than controls, reporting that subjects in the lowest quartile of selenium are eleven times more likely to have migraine compared with those in the top quartile [14]. Given the role of oxidative stress in the pathogenesis of migraine [15, 16], selenium may have a beneficial effect on migraine outcomes. However, despite evidence on the beneficial effects of selenium supplementation on other neurodegenerative diseases such as cognitive disorders [17], there has been no study assessing the effect of selenium supplementation on migraineurs.

### Objectives {7}

The present study aims to investigate the effect of selenium supplementation on oxidative stress, mental health and clinical symptoms in migraine patients.

### Trial design {8}

A randomized, parallel, two-arm, double-blind, and placebo-controlled superiority clinical trial will be conducted.

## Methods: Participants, interventions, and outcomes

### Study setting {9}

The present study will be conducted at the neurology clinic of Al-Zahra Hospital, affiliated with Isfahan University of Medical Sciences, Isfahan, Iran.

### Eligibility criteria {10}

#### Inclusion criteria

Participants who (1) have a confirmed migraine diagnosis according to the International Classification for Headache Disorders (ICHD-3) criteria [18] by an expert neurologist, (2) are aged between 18 and 65 years, and (3) experience at least two migraine attacks per month, will be included. No restrictions on the type of migraine will be considered; thus, patients with all types of migraine headaches, including migraine with/without aura and episodic/chronic migraine headaches, will be included.

#### Non-inclusion criteria

Participants who (1) are pregnant or lactating; (2) have consumed antioxidant supplements in the last three months; (3) have a medical history of infectious disorders, autoimmune disorders, diabetes mellitus, cardiovascular diseases, or any other neurological disorders such as other subtypes of headaches (i.e. tension-type headache, etc.), epilepsy, Parkinson’s and multiple sclerosis, or (4) are current smokers, will not be included.

#### Exclusion criteria

Participants who (1) suffer from complications related to selenium supplementation, (2) change the type or dosage of their medications during the intervention, and (3) are not willing to continue the intervention, will be excluded. 

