### Criteria for discontinuing or modifying allocated interventions {11b}

Participants will be free to withdraw from the study at any time. In addition, subjects may be withdrawn at the discretion of the investigator if the subject is non-compliant with the protocol. Further detailed information will be explained in the study results.

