### Procedure for unblinding if needed {17b}

Labels on supplement packs will be revealed only after the study completion. However, based on the criteria of the Medical Ethics Committee, unblinding is allowed in case of any adverse events to determine whether the patient received selenium or placebo. If so, it will be recorded and reported in the Iranian Registry of Clinical Trials, and the Ethics Committee of Isfahan University of Medical Sciences, as well as results of the study. Further information will also be collected to decide whether those who reported adverse side effects should be excluded.

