## Statistical methods

### Statistical methods for primary and secondary outcomes {20a}

To examine normal distribution of variables, the Kolmogorov–Smirnov test will be used. To normalize the non-normally distributed variables, we will conduct a log transformation. The intention-to-treat (ITT) approach will be used to estimate missing values on outcome variables. Independent sample t-test will be used to detect differences in quantitative variables between intervention and control groups. For the assessment of qualitative variables between the two groups, the chi-square test will be performed. The paired-sample t-test will also be used to examine within-group differences. One-way analysis of covariance (ANCOVA) will be performed to detect the effect of selenium supplementation on outcome variables. In this analysis, potential confounders will be taken into account. All statistical analyses will be conducted using the SPSS software version 21 (SPSS, Inc. Chicago, IL, USA). P-values less than 0.05 will be considered statistically significant.

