### Interim analyses {21b}

No interim analyses are planned for the present study; however, immediate study cessation will occur for those with adverse side effects. These adverse side effects include death, disability, and severe allergic reactions, which have a significant impact on the patient's health. However, as the ITT analysis will be performed, participants who drop out will also be included in data analysis.

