### Methods in analysis to handle protocol non-adherence and any statistical methods to handle missing data {20c}

In the present study, participants who drop out will not be excluded from the final analysis as an ITT method will be conducted. Missing data will be addressed by multiple imputations.

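### Exclusions after randomisation are not reconciled with the promised intention-to-treat analysis, and one kind may be decided once the arm is known

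*Protocol article*

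**What the plan says.** **Exclusion criteria.** This list is separate from the non-inclusion criteria and concerns events after entry. It names participants who "suffer from complications related to selenium supplementation" and those who "change the type or dosage of their medications during the intervention, and (3) are not willing to continue the intervention, will be excluded".

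**Section {11b}.** Here the wording is permissive: "subjects may be withdrawn at the discretion of the investigator if the subject is non-compliant with the protocol".

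**Section {17b}.** The article states that "unblinding is allowed in case of any adverse events to determine whether the patient received selenium or placebo". It then adds: "Further information will also be collected to decide whether those who reported adverse side effects should be excluded". No criterion for that decision is given.

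**Analysis.** Section {21b}, just after describing cessation for adverse effects, says that "as the ITT analysis will be performed, participants who drop out will also be included in data analysis". Section {20c} says that "participants who drop out will not be excluded from the final analysis as an ITT method will be conducted" and names multiple imputation for missing data. Section {20a} says: "The intention-to-treat (ITT) approach will be used to estimate missing values on outcome variables". The Methods part of the Abstract describes ITT in the same way.

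**The concern.** Randomisation protects the comparison only if everyone randomised is analysed in the allocated arm. The listed events happen after randomisation and can be linked to outcome and arm.

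- **Medication change.** It can be a response to the headache course, and section {12} makes clinical symptoms part of the primary outcome.
- **Complications.** The criterion is worded by reference to the active treatment. While blinding holds, a placebo patient's event could be classed the same way. Once the arm is disclosed, it may not be.
- **Adverse-event reporters.** Exclusion can be decided after the arm is revealed and without a rule, so the decision is open to selection.

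If such participants leave follow-up or the analysis, the arms compared are no longer those that were randomised. The text that should settle the matter is itself imprecise. ITT defines who is analysed and in which arm. It does not estimate missing values.

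**Working it through.** **1. The passages side by side**

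| Participant | Rule on exclusion | Kept by the ITT sentences? |
|---|---|---|
| Unwilling to continue | Exclusion criteria: mandatory | Yes, as a dropout ({20c}, {21b}). The wording conflicts unless *excluded* means only leaving treatment |
| Changes medication, keeps taking tablets and attends | Exclusion criteria: mandatory | Not clearly, as this person has not dropped out |
| Selenium complication | Exclusion criteria: mandatory | Yes if the person drops out ({21b}); otherwise not stated |
| Reports an adverse effect, possibly unblinded | {17b}: left open, no criterion | Not stated for a person excluded by that decision |
| Non-compliant | {11b}: discretionary withdrawal | Yes if withdrawal counts as dropping out; not stated |

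The second and fourth rows are the weakest. Nothing in the analysis sections clearly brings those participants back.

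**2. How large could the bias be?**

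The plan gives no exclusion rates, so this is illustration only. From the protocol: 36 per arm and the multiplier 1.96. Assumed: no true effect; outcome SD 1, with higher values worse; fractions e_S (selenium) and e_P (placebo) dropped from the analysis; dropped patients m SD worse than retained ones, with the same m in both arms.

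The overall mean is 0 in each arm, so the retained mean is −e·m. The selenium-minus-placebo difference then shifts, in size, by

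b = m(e_P − e_S)

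with SE = √[1/(36(1 − e_S)) + 1/(36(1 − e_P))]

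and type I error = Φ(−1.96 + b/SE) + Φ(−1.96 − b/SE).

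| e_S | e_P | m | b (SD) | SE | Type I error |
|---|---|---|---|---|---|
| 10% | 10% | 0.5 or 1.0 | 0 | 0.249 | 5.0% |
| 5% | 15% | 0.5 | 0.05 | 0.249 | 5.5% |
| 5% | 15% | 1.0 | 0.10 | 0.249 | 6.9% |
| 5% | 25% | 0.5 | 0.10 | 0.257 | 6.7% |
| 5% | 25% | 1.0 | 0.20 | 0.257 | 12.1% |

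Example, last row: b = 1.0 × (0.25 − 0.05) = 0.20; SE = √(1/34.2 + 1/27) = 0.257; b/SE = 0.777; Φ(−1.183) + Φ(−2.737) = 0.118 + 0.003 = 0.121.

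Swapping the rates between arms reverses the sign of b. Equal rates remove the bias only if the excluded patients are also alike in outcome: with 10% excluded in both arms but m = 1.0 in one and 0.5 in the other, b = 0.10 × (1.0 − 0.5) = 0.05 SD.

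**3. Why b is not set against the planned effect**

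The sample-size section labels 4.00 both as variance and as SD, for a difference of 1.4 − (−0.13) = 1.53. Its formula gives 2 × 2.802² × 16 / 1.53² = 107.3, so 108 per group, if 4.00 is the SD. It gives 2 × 2.802² × 4 / 1.53² = 26.8, so 27, if 4.00 is the variance. Neither is the stated 33, which would need an SD of about 2.22. The planned effect is therefore 1.53/4.00 = 0.38, 1.53/2.00 = 0.77 or 1.53/2.22 = 0.69 SD, depending on the reading. A fraction of it would mean little.

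**The case against.** **The benign reading.** The exclusion list sits under eligibility and does not mention analysis. Unwillingness to continue describes leaving treatment. The two sections that do address analysis keep dropouts, one of them directly after discussing cessation for adverse effects. So *excluded* can be read as stopping participation only. This stands: the text does not prove that anyone is removed from the analysis. But that reading is nowhere stated, and it leaves open the medication changer who stays and the decision after unblinding.

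**Stronger readings that a reader might infer.** The documents do not support these:

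- *All four groups are to be excluded.* Non-compliant participants may be withdrawn at discretion, and for adverse-event reporters the question is left open.
- *Excluded patients have no week-12 measurement.* No section says so. Section {33} plans blood at baseline and at the end of the intervention and does not say that sampling ceases.
- *Multiple imputation cannot repair the loss.* It may not. That depends on what drives the missingness and what the imputation model contains, and an article may leave the latter to a fuller document.
- *The bias is a large share of the planned effect.* Dropping the worst 20% of placebo and the worst 5% of selenium patients would shift the difference by 0.24 SD, but only if exclusion tracked the analysed outcome perfectly. With a correlation of 0.3 the shift is 0.3 × 0.24 = 0.07 SD. The rates are invented, and MDA, the variable used for the sample size, is a serum marker that need not follow the headache course.

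**Timing.** The protocol version is dated 17 February 2024 and the last visit was expected on 29 February 2024, so lost visits cannot generally be recovered. This limits the remedy for follow-up, but not for the analysis set.

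**Conclusion.** The point holds as an unreconciled rule about who is kept, with a risk of bias that is not shown to occur. The exclusion list and section {17b}, followed literally, can break the randomised comparison, and the ITT sentences do not clearly prevent it. The concern bites only if *excluded* means from follow-up or analysis. Its size and direction are unknown. It is zero if exclusions are alike in both arms, in rate and in the outcomes of those excluded. In the assumed scenarios with unequal rates it is 0.05 to 0.20 SD. Because the document states these rules itself and they do not fit together, this is not a detail merely left to an analysis plan.

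**What to change.** 1. State that the events under Exclusion criteria and in sections {11b} and {17b} remove nobody from the analysis set, and that every randomised participant is analysed in the allocated arm.
2. Use week-12 data wherever they were or can still be collected, whatever happened to tablets or medication.
3. Delete the {17b} sentence on deciding exclusion, or limit it so that it cannot affect the analysis set.
4. In the Abstract and section {20a}, say that ITT defines the analysis set. Reserve the multiple imputation of {20c} for values that could not be obtained.
5. Present any analysis without medication changers as a sensitivity analysis only.
6. Reconcile the stopping triggers. The exclusion list speaks of complications related to selenium, section {21b} names death, disability and severe allergic reactions, and section {22} refers to any complications. Which rule applies is for the sponsor to settle.

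**Cost.** Mostly wording, plus week-12 assessments where these are still possible. The effect estimate will include participants who stopped tablets or changed medication. Those who left before the change may have no week-12 data and will depend on imputation.

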### Who will take informed consent? {26a}

Each participant will be informed about the purpose, benefits and risks of the investigation by the principal investigator (AB) to obtain written informed before participation.

### Additional consent provisions for collection and use of participant data and biological specimens {26b}

Participants will be requested to provide consent for the review of their medical records and blood sample collection to assess oxidative stress biomarkers, including nitric oxide (NO), total antioxidant capacity (TAC), total oxidant status (TOS), and malondialdehyde (MDA). Participants will also provide consent for using their data in future publications, which is not obligatory.

## Interventions

### Explanation for the choice of comparators {6b}

Participants will be randomly assigned to either the intervention or placebo group. The intervention group (*n* = 36) will receive a daily tablet containing 200 µg selenomethionine for 12 weeks. In parallel, the placebo group (*n* = 36) will receive a tablet containing 200 µg starch per day for 12 weeks.

### Intervention description {11a}

After the recruitment of participants, they will be randomly assigned to either group. Participants in the intervention group will receive a tablet containing 200 µg selenomethionine daily for 12 weeks. Those in the placebo group will receive a tablet containing 200 µg starch per day. Starch was chosen given its easily digestible, and has a similar appearance and taste to selenium. The selenium and placebo tablets will look identical, having the same shape, color, and size. To maintain the study's integrity, an unbiased person will label the packs as A or B without knowing the contents. Participants will be asked not to change their lifestyle, including physical activity, dietary habits, and medication during the study. Clear instructions will also be provided on how to use their supplements. To monitor progress and address any concerns, participants will have phone check-ins every two weeks to track supplement consumption and assess for potential side effects.

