### Sample size {14}

The sample size was calculated based on means and standard deviations for the primary variable, which is MDA levels, reported in the study of Razavi et al. [19], considering a type I error of 5% (α = 0.05) and type II error of 20% (β = 0.20, power = 80%). Sample size was calculated using the following formula [20]:$$n=\frac{2{(\mathrm{a }+\mathrm{ b})}^{2} {\upsigma }^{2}}{{(\upmu 1 -\upmu 2)}^{2} }=33$$

*n* = the sample size in each group.

μ1 = the mean for malondialdehyde in the intervention group: -0.13 μmol/L based on the study of Razavi et al. [19]).

μ2 = the mean for malondialdehyde in the control group: 1.4 μmol/L based on the study of Razavi et al. [19]).

σ = the variance (SD) for mean concentrations of malondialdehyde: 4.00 (the average SDs reported for malondialdehyde in the control and intervention groups of Razavi et al.’s study [19]).

a = the conventional multiplier for alpha = 0.05 that was 1.96.

b = the conventional multiplier for power = 0.80 that was 0.842.

Based on the formula, we will need a sample size of 33 for each group. Considering a drop-out rate of 10%, we plan to recruit 36 migraine patients in each group.

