### Concealment mechanism {16b}

An independent person who is not involved in the trial will label supplement packs as A and B. Both the investigators who are performing the study and participants will be blinded to the intervention allocation. Additionally, the allocation sequence will be concealed from those who are assigning participants to the intervention groups using opaque sealed envelopes. Randomization codes will be unlocked after the trial completion.

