## Assignment of interventions: Blinding

### Who will be blinded {17a}

The current study will have a double-blind design, which means that both the investigators who are performing the study and participants will be unaware of group allocation.

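### With two pack letters for two arms, one code break can reveal the arm of every patient whose letter is known, and the plan does not limit who learns the result

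*Protocol article*

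**What the plan says.** The pack labels are described twice. Intervention description {11a} says that "an unbiased person will label the packs as A or B without knowing the contents". Concealment mechanism {16b} says: "An independent person who is not involved in the trial will label supplement packs as A and B". Neither section mentions a number or code specific to a patient.

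The trial has two parallel arms (Trial design {8}), and Sample size {14} states "we plan to recruit 36 migraine patients in each group", so 72 in all.

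On blinding, Who will be blinded {17a} promises that "both the investigators who are performing the study and participants will be unaware of group allocation". Section {16b} adds: "Randomization codes will be unlocked after the trial completion". Procedure for unblinding {17b} opens with the general rule "Labels on supplement packs will be revealed only after the study completion". It then makes an exception: subject to the criteria of the Medical Ethics Committee, "unblinding is allowed in case of any adverse events to determine whether the patient received selenium or placebo". A break is to be recorded, reported to the trial registry and the ethics committee, and included in the study results. The section does not say who else may learn the result, or who may not.

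**The concern.** The exception in {17b} is written as if one patient could be unblinded alone. That works when each patient has a separate code. When all patients in an arm share a letter, the answer for one patient is the answer for the whole arm, and by elimination for the other arm too.

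The outcomes at stake are those that knowledge of treatment can shift. Headache severity on the VAS is rated by the patient, and a neurologist assesses the severity, frequency and duration of attacks. HIT-6, MSQ and DASS-21 are questionnaires. Clinical symptoms are part of the primary outcome in Outcomes {12}; quality of life and mental health are secondary. The double-blind description would be weakened for these outcomes in any patient assessed after a break that reached that patient or the assessor.

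**Working it through.** The plan states no figure on this point, so there is none to reproduce. The check has a logical part, an illustrative probability and a date calculation.

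**1. How many allocations one break can reveal**

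Inputs: 2 letters ({11a}, {16b}), 2 arms ({8}), 36 patients per arm ({14}).

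- Total: 36 + 36 = 72.
- Patients sharing the unblinded patient's letter, that patient included: 36.
- Patients with the other letter, identified by elimination: 36.
- Revealed to someone who learns the result and knows every patient's letter: 36 + 36 = 72 of 72.
- With 72 unique codes: 72 / 72 = 1 patient per code, so 1 of 72.

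The figure of 72 is an upper limit. It counts only patients whose letter is known to the person who learns the result; a later patient is added once that patient's letter is known.

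**2. The rules side by side**

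- {16b} gives the time for unlocking codes as after completion, without exception.
- {17b} gives the same time for the labels, then allows an earlier break for one patient.
- With shared letters, that earlier break discloses what both labels mean. The exception cannot be confined to one patient, so it overrides the rule it follows. With patient-specific codes the two sentences would be compatible.

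**3. Chance of at least one break**

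The documents give no rate. Let p be an assumed per-patient chance of an adverse event that leads to a code break, independent across patients. Then P(at least one break) = 1 − (1 − p)^72.

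| Assumed p | 1 − (1 − p)^72 |
|---|---|
| 0.1% | about 7% |
| 0.5% | about 30% |
| 1% | 0.515, about 52% |
| 2% | 0.767, about 77% |
| 5% | 0.975, about 98% |

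**4. What can still be changed**

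Trial status dates this protocol version 17 February 2024 and expects the last visit on 29 February 2024. Treatment lasts 12 weeks, with tablets handed out in weeks 1 and 6 ({11c}). For a last visit on 29 February, the week-6 supply falls about 6 weeks (42 days) earlier, around 18 January 2024. That is about a month before this version. If the schedule held, few or no packs remained to be dispensed.

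**The case against.** Several points on the other side are fair.

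- **The article is condensed.** A pack number could exist in the full protocol, so it is an inference that A or B is the only code. The inference is reasonable because two sections describe the labelling and neither mentions another code, but it is not certain.
- **The trigger is qualified.** Unblinding is permitted, not required, and depends on ethics committee criteria that are not shown. Interim analyses {21b}, in the context of stopping, describes adverse side effects as death, disability and severe allergic reactions. A reader might infer that every minor complaint leads to a break; the text does not establish that. This is why the table starts at 0.1%.
- **A break is not the same as bias.** A reader might take the percentages as the chance that the whole trial is unblinded. They are the chance of at least one break. Bias also requires that patients or assessors learn the result, know the letters, and have assessments still to come. The recipients named in {17b} do not include the assessing neurologist. That section does not exclude the neurologist either.
- **Biomarkers are less exposed.** MDA, the variable used for the sample size, and the other oxidative stress markers are laboratory assays. The concern covers only part of the primary outcome.
- **Upcoming allocations.** A reader might infer that a break also discloses the next assignment. The documents do not support this: {16b} uses opaque sealed envelopes, and knowing what A means does not reveal which letter comes next.
- **Timing of the key.** A reader might infer that the codes are opened before the analysis. The text says only after completion. It does not place the opening before or after the analysis, and that order is commonly left to the full protocol or analysis plan.

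None of this removes the core problem, which is a shared two-letter code, a permitted mid-trial break, and no stated limit on who learns the result.

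**Conclusion.** The point holds as a weakness in the blinding procedure that should be corrected. As described, one code break can reveal up to 72 of 72 allocations instead of 1 of 72, and it cannot be squared with the rule that labels are revealed only after completion. The logic rests on one assumption: that no patient-specific pack code exists beyond the letters the article describes.

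The possible harm is limited to the VAS, attack frequency and duration, HIT-6, MSQ and DASS-21 in patients assessed after a break, and only if patients or assessors come to know of it. Patients who had completed their assessments before a break are unaffected. How likely a break is cannot be determined from the documents: the range of about 7% to 98% reflects the assumed rates alone. Nothing in the documents shows that a break took place.

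**What to change.** 1. **Packs still to be dispensed, if any:** replace the letters with patient-specific codes tied to the randomisation list, so that a break opens one patient only. On the stated dates this probably applies to few or no packs.
2. **Packs already labelled A or B:** have the independent person who holds the key disclose a break only outside the outcome-assessment and analysis team. Name that person's role, because {11a} describes the labeller as not knowing the contents. Which events justify a break is a clinical matter on which this point takes no position.
3. **Log:** record each break with its date and everyone who learned the result. If there was none, say so in the report.
4. **Sensitivity analysis:** if a break occurred, report the self-reported and neurologist-assessed outcomes with and without patients assessed after the first break.
5. **Masked analysis:** run the main analysis on the A/B codes before the key is opened, and state this order.
6. **Wording:** reconcile {16b} and {17b}, so that the rule on opening codes and labels and its exception can both be followed, with the exception stating who may be told.

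The cost is a little administrative work, a few sentences of protocol text and, if a break occurred, one sensitivity analysis. Sample size and visits do not change.
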